## Abstract

**Introduction:**

Parkinson’s disease is the second most common chronic neurodegenerative condition with bladder dysfunction affecting up to 71%. Symptoms affect quality of life and include urgency, frequency, hesitancy, nocturia and incontinence. Addressing urinary dysfunction is one of the top 10 priority research areas identified by the James Lind Alliance and Parkinson’s UK.

**Objectives:**

Conduct a randomised controlled trial (RCT) targeting people with Parkinson’s disease (PwP) who have self-reported problematic lower urinary tract symptoms, investigating the effectiveness of transcutaneous tibial nerve stimulation (TTNS) compared with sham TTNS. Implement a standardised training approach and package for the correct application of TTNS. Conduct a cost-effectiveness analysis of TTNS compared with sham TTNS.

**Methods and analysis:**

An RCT of 6 weeks with twice weekly TTNS or sham TTNS. Participants will be recruited in 12 National Health Service neurology/movement disorder services, using a web-based randomisation system, and will be shown how to apply TTNS or sham TTNS. Participants will receive a weekly telephone call from the researchers during the intervention period. The trial has two coprimary outcome measures: International Consultation on Incontinence Questionnaire-Urinary Incontinence Short Form and the International Prostate Symptom Score. Secondary outcomes include a 3-day bladder diary, quality of life, acceptability and fidelity and health economic evaluation. Outcomes will be measured at 0, 6 and 12 weeks.

A sample size of 208 randomised in equal numbers to the two arms will provide 90% power to detect a clinically important difference of 2.52 points on the Internatioanl Consultation on Incontinence Questionnaire - Short Form (ICIQ-SF) and of 3 points in the International Prostate Symptom Score total score at 12 weeks at 5% significance level, based on an SD of 4.7 in each arm and 20% attrition at 6 weeks. Analysis will be by intention to treat and pre defined in a statistical analysis plan

**Ethics and dissemination:**

East of Scotland Research Ethics Service (EoSRES), 18/ES00042, obtained on 10 May 2018. The trial will allow us to determine effectiveness, safety, cost and acceptability of TTNS for bladder dysfunction in PWP. Results will be published in open access journals; lay reports will be posted to all participants and presented at conferences.

**Trial registration number:**

ISRCTN12437878; Pre-results.

Strengths and limitations of this studyFully powered randomised controlled study.Participants may become unblinded.Participants may want to switch arms.

## Introduction: background and rationale

### Lower urinary tract (LUT) symptoms in Parkinson’s disease

Parkinson’s disease is characterised predominantly by the motor complaints of bradykinesia, rigidity, rest tremor and gait disturbances. However, non-motor symptoms (NMS) are a common accompaniment^1^ with LUT symptoms reported in 38%–71% of people with Parkinson’s disease (PwP).^2^ These LUT symptoms are an important cause of morbidity and have a major impact on early institutionalisation and health-related costs.^3^ There also exists an association between nocturia and the risk for falls and hip fractures.^4–7^

Current treatments for LUT dysfunction in PwP are limited. It is likely that levodopa and other Parkinson’s medication affect bladder function; however, studies evaluating the effects of these medications on micturition have produced conflicting results.^8^ Currently, PwP may be offered advice on fluid intake and on behavioural treatment such as habit training or timed voiding with or without pelvic floor muscle training, but the evidence base supporting these techniques is limited.^9–13^ Antimuscarinic medication, competitively antagonise muscarinic acetylcholine receptors, resulting in detrusor relaxation, lower intravesical pressures and reduced storage symptoms. However, it has been found that PwP often discontinue their use due to side effects of nausea, dry mouth and constipation.^11^ More importantly, there is evidence to suggest a worsening in cognition and consciousness in susceptible neurological patients, and caution in prescribing is advised.^10 14^ Intravesical injections of botulinum toxin into the detrusor is sometimes considered in PwP and has been described in four small studies to date,^15–18^ which reported some improvement in symptoms.

For the reasons discussed, there is a need to explore options that are non-invasive and associated with minimal side effects.

### Patient involvement

A focus group of patients and carers of PwP and clinicians involved in treatment was held in London in 2017. During this meeting, the impact of bladder dysfunction on quality of life (QOL) was highlighted and also the lack of effective interventions. Transcutaneous tibial nerve stimulation (TTNS) was identified as a treatment option they would be willing to use, and a treatment regimen of twice weekly stimulation sessions for 6 weeks was preferred from the point of view of compliance, acceptability and practicability. We also have PwP on our trial steering committee, and they have advised us on the content of our participant facing literature and protocol.

### Tibial nerve stimulation (TNS): a form of neuromodulation

Neuromodulation has been used increasingly to treat urinary disorders through stimulation of the sacral, pudendal, tibial and genital nerves. The most often studied neuromodulation routes for overactive bladder (OAB) have been the sacral nerve roots and the tibial nerve (TN).^17^ Nerve fibres in the TN represent the L4-S3 spinal segments and therefore share a similar origin as the innervation to the bladder, rectum, anal sphincter and pelvic floor.^19^ The precise mechanism of action of neuromodulation is unclear, but it is thought to modulate the sacral plexus indirectly via the sensory, motor and autonomic fibres of the TN.^19^ Percutaneous TNS (PTNS) stimulation involves a qualified healthcare provider inserting a small needle just behind the medial malleolus to conduct the current from the small hand held stimulator. This is a ‘minimally’ invasive neuromodulation technique that is recommended by National Institute for Health and Care Excellence (NICE)^19^ for the treatment of OAB symptoms when conservative options have failed and is increasingly offered in hospital and urology services, requiring the patient to come into clinic for each treatment session (usually 12 weekly sessions). In comparison, much less is known about the effects of TTNS using the non-invasive transcutaneous route, which involves the delivery of the stimulation using surface electrodes that can be applied by the patient themselves and that can be used in the person’s home. TTNS is potentially more accessible and may enable PwP to self-manage and feel more in control of their care. It is also less costly than other stimulation modalities.

### Evidence

As stated above, TNS is a form of peripheral neuromodulation targeted towards symptom relief of OAB and urge urinary incontinence.^20^ The authors reviewed the literature relating to the use of TTNS or PTNS in the neurogenic population and identified one study with spinal cord patients in which the use of TTNS (n=50) was compared with solifenacin succinate (n=50). Both groups improved significantly in all bladder diary measurements, but there were fewer side effects with TTNS.^21^ Seth *et al*
22 compared two different regimens of TTNS (Gp1: 30 min daily; Gp2: 30 min weekly, for 12 weeks) between 24 patients with multiple sclerosis (PwMS) with OAB to 24 people with idiopathic OAB. Significant improvements in symptoms were reported for both groups. Another prospective study looked at TTNS in 70 PwMS with OAB over a 3-month period demonstrating efficacy of reduced urinary urgency and frequency as well as other secondary outcomes such as improved QOL and reduced burden.^23^ Several studies have reported TTNS use to be safe, acceptable and potentially beneficial in regards to LUT symptoms in PwMS in their own homes, older adults in care homes and stroke patients in their own homes,^22 24 25^ respectively. More recently, a study with 68 participants with overactive detrusor persisting after first-line or second-line treatments in a non-superiority trial reported no difference in efficacy between PTSN and TTNS.^26^

Studies specific to PwP and PTNS or TTNS are limited. Kabay *et al*
27 reported on a non-randomised study with 47 PwP and PTNS and found significant improvement in symptoms and urodynamic parameters. Only two small studies were identified with PwP using TTNS.^28 29^ Ohannessian *et al*
28 demonstrated that five out of six female PwP with OAB, who used TTNS for 6 weeks, considered TTNS to be effective. The study also implied that TTNS has potential efficacy of improving urodynamic and symptom scores in this population. Perissinotto *et al*
29 reported a study comparing TTNS and placebo stimulation in 13 PwP presenting with LUT symptoms. They demonstrated that TTNS holds promise as an option in the treatment of LUT symptoms in this population reducing urgency and nocturia and improving QOL.

The findings of this review have identified that TNS using the transcutaneous route (TTNS) is a feasible option for PwP, but efficacy has not been determined. A study is currently underway in France evaluating a TTNS regimen of 20 min daily stimulation for 90 days in a mixed group of patients with Parkinson’s disease and multiple system atrophy (MSA)^30^ Liaising with the Principle Investigator, recruitment into the study appears to be satisfactory. Considering that LUT dysfunction in Parkinson’s disease and MSA is distinctly dissimilar, we have chosen to study the effects of TTNS in Parkinson’s disease alone. Patient notes will be screened if the diagnosis is unclear. In addition, our consultation group of PwP and carers unanimously preferred a treatment regimen of twice weekly stimulation sessions for 6 weeks rather than daily sessions over 3 months from the point of compliance, acceptability and practicability. For this reason, we will investigate the most commonly used and evaluated treatment protocol for TNS involving 12×30 min stimulation sessions over 6 weeks.

It is hypothesised that the effectiveness and cost-effectiveness of a strategy of TTNS is superior to sham TTNS at 12 weeks.

### Objectives

The Stimulation of the tibail nerve for urinary incontinence in Parkinson's (STARTUP) trial will determine/undertake the following:

Conduct a randomised controlled trial (RCT) targeting PwP who have self-reported problematic LUT symptoms, investigating the effectiveness of TTNS compared with sham TTNS.Implement a standardised training approach and package (already developed) for the correct application of TTNS.Conduct a cost-effectiveness analysis of TTNS compared with sham TTNS.Assess fidelity to the TTNS intervention and any research participation effects in the intervention and placebo stimulation groups.

### Trial design

The present study is a multicentred, parallel group, superiority, double-blind RCT comparing the effectiveness of an experimental strategy of twice weekly use of active TTNS for 6 weeks against a twice weekly use of sham TTNS for 6 weeks in PwP and LUT symptoms. Randomisation is at a 1:1 ratio for the two arms of the trial.

### Study setting

Routine care setting for Parkinson’s patients in the UK.

### Eligibility criteria

#### Inclusion criteria

Patients of 18 years of age and above (no upper age limit), with a diagnosis of Parkinson’s diesase(any stage) with self-reported problematic LUT symptoms.Capacity to consent/complete self-report outcome measures: ability to apply TTNS (or placebo) independently or has carer who can apply for durationStable Parkinson’s medication for 3 months.Participants may be treatment naïve, failed or continuing treatment with antimuscarinic medication (group allocation will be minimised to account for these groups).Patients who are being treated, or have been treated, for benign prostatic hyperplasia or prostate cancer can be included at the discretion of the PI.Patients taking medications such as alpha-blocker medicines (prazosin, indoramin, tamsulosin, alfuzosin, doxazosin and terazosin), or 5-alpha reductase inhibitor medicines. Finasteride and dutasteride can be included. Patients taking approved treatment for prostate cancer, or example, apalutamide and enzalutamide, bicalutamide, Casodex, Zytiga, Lupron Depot, Xtandi and Zoladex can be included at the discretion of the PI.Patients who have had or are having treatment for cancer, for example, urological cancer can be included on an individual basis at the discretion of the PI.

#### Exclusion criteria

Pacemaker or implanted electrical device, including deep brain stimulation.Unable to understand the instructions relating to the bladder diary and/or the use of the stimulator or does not have a relative willing to help.Ulceration or broken skin, in area of pad placement.History of peripheral vascular disease and epilepsy.Current urinary tract infection (if suspected by symptoms refer to General Practitioner and can recruit once cleared).Receipt of botox for bladder symptoms or TTNS within the last year.

### Who will take informed consent?

All participants will undergo a process of informed consent that will include the delivery of balanced written information concerning the need and overall benefit of the trial followed up by discussion with a local STARTUP researcher. This discussion will include a check of understanding concerning benefits and risks of participation and ensuring that participants accept that the treatment will be allocated at random regardless of any personal preference they may have.

Please see online supplementary material to review the consent form.

10.1136/bmjopen-2019-034887.supp1Supplementary data

### Additional consent provisions for collection and use of participant data and biological specimens

Not applicable.

## The intervention

There is a risk of participant unblinding if the intervention or sham intervention is discussed in detail within this protocol; this will be published before trial recruitment is complete. The authors recognise the importance of the allocated intervention being accepted by the participant as the active intervention and have developed the sham intervention to be as realistic as possible yet delivering no intervention.

The treatment protocol developed by Amarenco *et al*
31 will be adopted for this trial.

All participants will use the stimulator for two 30 min sessions a week for 6 weeks. It is preferable to have 2–4 days between stimulation sessions.

A training protocol, including a manual for clinicians and instruction leaflets for participants, has been developed. Participants will be instructed to use the TTNS device twice weekly for 6 weeks with weekly telephone support by research staff.

### Criteria for discontinuing or modifying allocated interventions

There are no special criteria for discontinuing or modifying allocated interventions. Participants may choose to stop doing the active or sham TTNS themselves for any reason.

### Strategies to improve adherence to interventions

None beyond normal encouragement.

### Relevant concomitant care permitted or prohibited during the trial

No special provisions.

### Provisions for post-trial care

None beyond standard care within the National Health Service (NHS). Agreed to show how to set the parameters should the participants want to buy a unit.

### Outcomes

The outcome measures and other data to be collected are summarised in table 2.

**Table 2 T2:** Summary of data collection

	Baseline (week 0)	Week 6–7 (on completion of intervention period	Week 12
ICIQ-UI SF	×	×	×
IPSS	×	×	×
3-day (24 hours) bladder frequency chart	×	×	×
Qualiveen	×	×	×
PDQ-8	×	×	×
Resource questionnaire		×	×
Change in medication	Weekly		×
Exit questionnaire		×	
Compliance downloaded		×	

ICIQ-UI SF, International Consultation on Incontinence Questionnaire-Urinary Incontinence Short Form; IPSS, International Prostate Symptom Score; PDQ-8, Parkinson’s Disease Questionnaire-8 items.

To decrease burden on participants (ie, only one visit), the baseline outcome data will be collected at the visit to clinic/home following completion of consent, randomisation and instruction on use of device.

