### Participant timeline/pathway

The steps within the trial that the participants will take are summarised in box 1.

Box 1The participant pathwayParticipant’s identified at clinic by local PIs, Parkinson’s nurses or research nurses.

Participant information leaflet with expression of interest form attached given/sent to patient along with preaddressed envelope.

Posters also to be put up in relevant clinics to inform patients.Potential participants opt in either by phoning the trial office or by returning the expression of interest form to them.

Staff at the trial office contact participant discuss further the implications of the study and complete screening log. If willing and eligible to be a participant, then the patient is allocated a participant study number and is given an appointment to attend the clinic or for the research nurse to visit them at home (confirmed by trial office with clinic)

At the clinic/home, the participant will be consented, the clinical assessment form will be completed, randomisation will be completed (using the web-based system) and then the participant will be shown how to use the stimulation/placebo stimulation and provided with written instructions.

The participant is given a pack to take home with them containing the 3-day bladder frequency diary (with simple instructions) and the questionnaire booklet. The participant is asked to complete the bladder frequency diary during the next 3 days (starting with the first morning void) before starting to use the stimulation. The pack also contains the bladder diary and a questionnaire booklet to be completed at 6 weeks. Prepaid addressed envelopes will be available.

During the 3 days at home, the research office telephones the participant to support completion of their bladder diary. The participant either completes the questionnaires themselves or over the telephone. These diaries are then posted to the research office. Date when the participant will start using the intervention agreed and the times of the weekly follow-up telephone calls agreed.

Trial office staff will telephone the participant weekly to see how things are going, ask about change in medications, adverse events and so on and will be available for any queries. Trial office will remind/help participant to complete the diary and questionnaires at the end of 6 weeks and will get the participant to unlock the compliance monitor before sending the unit back in the prepaid Jiffy bag.

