### Assignment of interventions: allocation

#### Sequence generation

Participants who provide written informed consent will be randomised using a computer generated system to either TTNS intervention or non-active stimulation arm and will be minimised on two factors: (1) severity of urinary symptoms, as reported at study baseline by the IPSS in the Clinical Assessment Form, that is, mild, moderate or severe; and (2) status on antimuscarinic medication, that is, treatment naïve, failed or continuing such treatment.

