### Assignment of interventions: blinding

#### Who will be blinded

Due to the nature of the intervention, the research team delivering the intervention will not be blinded to the treatment received; however, we have designed several different mechanisms by which participant allocation will be concealed. Participants will be blinded to group allocation. Outcome measures are primarily self-reported and submitted anonymously. Those involved in the data analyses and statistics will be blinded to the group allocation.

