### Data collection and management

#### Plans for assessment and collection of outcomes

Data will be collected via participant-completed questionnaires at baseline and at 6 and 12 weeks. A 3-day bladder frequency diary will be completed prior to baseline, at 6 and 12 weeks. Completed outcome data are retuned by post. Relevant demographic and medical history information will be collected at baseline.

Patient resource use questionnaires will also be completed by participant at home at 6 and 12 weeks.

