### Analysis of primary outcome measures

The analysis of the coprimary outcomes (ICIQ-UI SF score and IPSS score)^32 33^ will estimate the mean difference (and 95% CIs) between the experimental and comparator arms at 12 weeks postintervention using linear mixed models adjusting for minimisation covariates (reported symptom severity and treatment category), baseline ICIQ-UI SF/IPSS score and other potentially important prognostic covariates. Recruiting centre will be included in the models as a random effect.

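### Baseline ICIQ-UI SF is collected after randomisation and device training, yet it is a covariate in a coprimary model, so allocation can affect it

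*Protocol article*

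**What the plan says.** **Order of steps.** The note under Table 2 (Outcomes) states that "the baseline outcome data will be collected at the visit to clinic/home following completion of consent, randomisation and instruction on use of device", and gives lower participant burden (a single visit) as the reason. Box 1 (Participant timeline/pathway) has consent, then the clinical assessment form, and then "randomisation will be completed (using the web-based system) and then the participant will be shown how to use the stimulation/placebo stimulation". After that, "The participant is given a pack to take home with them containing the 3-day bladder frequency diary (with simple instructions) and the questionnaire booklet". On how the booklet is filled in: "The participant either completes the questionnaires themselves or over the telephone".

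**Blinding.** Under Who will be blinded, participants are blinded, but "the research team delivering the intervention will not be blinded to the treatment received".

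**Use in the analysis.** Analysis of primary outcome measures specifies linear mixed models "adjusting for minimisation covariates (reported symptom severity and treatment category), baseline ICIQ-UI SF/IPSS score", with other prognostic covariates and centre as a random effect.

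**IPSS before randomisation.** Sequence generation minimises on "severity of urinary symptoms, as reported at study baseline by the IPSS in the Clinical Assessment Form". Box 1 completes that form before randomisation.

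**Baseline diary.** Secondary outcome measures and Box 1 both place it after randomisation and before home use of the device. Plans for assessment and collection of outcomes says instead: "A 3-day bladder frequency diary will be completed prior to baseline, at 6 and 12 weeks".

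**The concern.** Adjusting for a baseline score is safe when allocation cannot have influenced it. Here the baseline ICIQ-UI SF, Qualiveen and PDQ-8 are completed once the participant has been allocated and trained on the active or sham unit by someone who knows which it is. Cues at training, staff manner or raised expectation could alter how symptoms are rated, and could do so differently by arm. The model would then remove part of a difference that allocation itself created, and the treatment estimate would move by a corresponding amount.

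This matters most for ICIQ-UI SF. It is a coprimary outcome, and no measurement of it before allocation is described. A later analysis plan cannot recover a score that was never taken. Under Box 1 the booklet is also posted back after allocation, so a missing baseline score is itself an event that occurs after randomisation.

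**Working it through.** **1. Sample size as stated (Sample size calculation).** Difference 2.52, SD 5, two-sided 5%, 90% power:

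n per arm = 2 × (1.960 + 1.282)² × 5² / 2.52² = 82.7, so 83 per arm and 166 in total. With 20% attrition, 166 / 0.8 = 207.5, so 208. The stated figure reproduces, and this point does not dispute it.

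**2. Bias formula.** Let s be the difference in mean baseline score (active minus sham) caused by allocation, and β the slope of outcome on baseline. In a baseline-adjusted model the treatment difference is biased by −β × s. Higher scores are worse, so the bias favours TTNS if the active arm reports higher baseline scores, and goes against TTNS if it reports lower ones.

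**3. Inputs.** From the article: SD 5, 83 analysed per arm, target difference 2.52. Not in the article, hence assumed: s = 0.5 to 1.0 point and β = 0.3 to 0.7. Baseline and follow-up SDs are taken as equal, so that β is also the correlation. Centre and the other covariates are ignored.

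**4. Standard error.** Unadjusted: 5 × √(2/83) = 0.776. Adjusted for baseline: 0.776 × √(1 − β²). At β = 0.5 this is 0.672.

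**5. Type I error.** With k = |bias| / SE, it is Φ(−1.96 + k) + Φ(−1.96 − k). The last column gives a simulation of the baseline-adjusted analysis (4,000 runs per cell), with shifts in both directions.

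| β | s | Absolute bias | % of 2.52 | Adjusted SE | Type I error, formula | Type I error, simulated |
|---|---|---|---|---|---|---|
| 0.3 | 0.5 | 0.15 | 6% | 0.740 | 5.5% | 5.4–5.7% |
| 0.3 | 1.0 | 0.30 | 12% | 0.740 | 6.9% | 7.0–7.1% |
| 0.5 | 0.5 | 0.25 | 10% | 0.672 | 6.6% | 6.5–7.1% |
| 0.5 | 1.0 | 0.50 | 20% | 0.672 | 11.5% | 11.3–11.8% |
| 0.7 | 0.5 | 0.35 | 14% | 0.554 | 9.7% | 9.4–9.7% |
| 0.7 | 1.0 | 0.70 | 28% | 0.554 | 24.4% | 23.2–24.6% |

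With s = 0 the simulated type I error is 4.7% to 5.5% and the estimate is unbiased. Using the unadjusted SE of 0.776 for β = 0.5 and s = 1.0 would give 9.9%. That is too low for a baseline-adjusted model, where 11.5% is the consistent figure.

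**6. Passages side by side.**
- Baseline questionnaires: at the visit (note under Table 2) against a take-home booklet, self-completed or done by telephone (Box 1). Both are after randomisation and training.
- IPSS: on the Clinical Assessment Form before randomisation (Box 1, Sequence generation). Table 2 also lists it among the baseline data that the note places after randomisation.
- Baseline diary: after randomisation (Secondary outcome measures, Box 1) against before baseline (Plans for assessment and collection of outcomes).

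**The case against.** **The order is deliberate, and participants are blinded.** The article discloses the order and its reason. The sham is designed to pass as active, and the questionnaires are self-reported. This stands as a limit on the concern: a shift needs cues from training or from staff contact, and the article gives no evidence of one. It does not remove the route, because the trainers know the allocation and the article itself lists participant unblinding as a limitation. A reader might infer that the primary result will be biased, or that error is inflated by one particular amount. The documents support neither. They support only that the covariate can be affected.

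**IPSS is covered.** This largely stands. A score from before randomisation exists, and the model also adjusts for the severity category derived from it. A reader might infer that there are certainly two baseline IPSS values and that leaving the choice open is an error. The booklet's contents are not itemised, and naming the covariate can be left to an analysis plan that is not shown.

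**Missing baselines are handled.** Partly so. The article plans to examine missingness, including by arm, and to use multiple imputation if necessary. It does not show that anyone with follow-up would lack a baseline.

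**The diary wording is peripheral.** Agreed. The diary is a secondary outcome and does not enter the coprimary models.

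**Conclusion.** The point holds for ICIQ-UI SF. Its only described baseline comes after allocation and after training by unblinded staff, and it is a covariate in a coprimary model. Qualiveen and PDQ-8 share the timing. IPSS needs only the use of the score already on the Clinical Assessment Form.

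Under the assumed shift and slope, the bias is 0.15 to 0.70 point (6% to 28% of 2.52) and type I error about 5% to 25%. At the lower end there is practically no inflation. The direction is unknown, and with no shift there is no bias. The article gives neither the shift nor the slope, so these figures show what is possible, not what is expected. The case for changing the order is that the risk is avoidable at little cost.

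**What to change.** 1. **Further participants:** keep the single visit, but complete the baseline ICIQ-UI SF, Qualiveen and PDQ-8 after consent and before randomisation and device training. The sample size of 208 does not change.
2. **IPSS:** use the Clinical Assessment Form score as the baseline covariate for everyone.
3. **Participants already recruited** (the first was randomised in October 2018): flag their ICIQ-UI SF baseline as taken after randomisation. Because the trial will then hold a mix of baselines from before and after randomisation, add a sensitivity analysis of the ICIQ-UI SF outcome that omits that score and adjusts for variables known before randomisation (Clinical Assessment Form IPSS and the minimisation factors).
4. **Text:** reconcile the note under Table 2 with Box 1 on where the questionnaires are completed. Correct Plans for assessment and collection of outcomes so that the baseline diary is described as after randomisation and before treatment.

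The cost is a few more minutes in clinic, a site instruction and a minor amendment. The sensitivity analysis may be less precise than one adjusted for baseline ICIQ-UI SF.
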